## Abstract

**Background/Objectives**: Simulation-based education often lacks personalization, focusing on technical competence rather than individual student profiles. This protocol describes a study designed to evaluate whether adapting gamified narratives to nursing students’ personality profiles has the potential to support academic performance in obstetrics. This study aims to validate the integration of psychometric profiling and AI as a sustainable strategy for personalized clinical training. **Methods**: A cluster-randomized controlled longitudinal pilot trial will be conducted at the University of Atlántico Medio. The protocol has been submitted for registration at ClinicalTrials.gov (Registration Pending). Thirty-eight second-year nursing students meeting inclusion criteria (excluding repeaters or those with prior specialized training) will be assigned by natural practice to either a control group (generic gamification) or an experimental group (gamification adapted according to Player Personality and Dynamics Scale profiles using AI-generated content). The intervention comprises four clinical simulation sessions focusing on pregnancy and childbirth, which are managed via the Wix platform. The primary outcome is academic performance, measured as “Learning Gain” (post-test scores minus pre-test scores). Secondary outcomes include student satisfaction measured via the Gameful Experience Scale. Data will be analyzed using Mann–Whitney U tests to compare overall efficacy and intragroup evolution. To minimize observer bias, knowledge assessments will utilize automated, objective scoring, and participants will be blinded to the study hypothesis. **Expected Outcomes**: The study aims to establish the technical and pedagogical feasibility of integrating AI-adapted narratives into nursing curricula. It is anticipated that the personalized approach will show positive trends in learning gains and engagement patterns, providing a baseline for larger multicenter trials. **Conclusions**: This protocol presents a framework for “Precision Education” in nursing, shifting from “one-size-fits-all” simulations to student-centered adaptive training. The use of Generative AI makes such personalization sustainable and cost-effective for health science faculties.

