### 2.7. Interventions

The intervention will be carried out in the nursing classroom of the Faculty of Health Sciences. It will be structured in four face-to-face sessions lasting 2 h each. The process will be led entirely by the PI, who will act as a teacher, clinical facilitator, and administrator of the gamified platform.

Prior to the start of the study, the digital learning environment will be developed: narrative scripts will be generated using generative AI tools. It is important to note that Generative AI is used exclusively offline during the pre-intervention design phase as a drafting tool for the narrative scripts. The AI does not interact with students in real-time, nor does it evaluate their clinical answers. All AI-generated texts are thoroughly reviewed, clinically curated, and validated by the PI prior to their integration into the Wix platform (Wix.com Ltd., Tel Aviv, Israel) to prevent any clinical hallucinations or biases. In the CG, the narrative will be linear and generic for each topic. In the EG, there will be five narrative variations per theme, adapted to the profiles of the PPDS (Tryhard, Coacher, Esthetic, Joker, and Toxic). To clarify the specific elements of adaptation and ensure reproducibility, Table 1 details the differences between the generic and adapted narratives. It is important to note that the level of clinical difficulty and the learning objectives remain invariant between groups to ensure the validity of the academic performance comparison: patient vital signs, clinical history, learning objectives, and multiple-choice questions are identical in both groups. The adaptation focuses exclusively on the narrative ‘wrapping’, the tone of the feedback, and the motivational mechanics (gamification elements) triggered by the Wix platform.

A master website will be set up on Wix. Progress will be managed through “Digital Locks”, where students will be required to solve clinical issues embedded in Google Forms. Upon submitting the correct answer, the form will return a password that will allow the student to unlock the next page (level) in Wix.

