-Satisfaction: The students’ subjective perception of the usefulness, fun, and motivation generated by the activity will be evaluated using the Gameful Experience Scale (GAMEX) [28]. This validated 27-item instrument in Spanish is suitable for measuring game experience in nursing students’ training. It uses Likert-type responses to measure the multidimensional nature of the gamified experience in the educational context. The six dimensions include enjoyment, abstraction, creative thinking, activation, absence of negative effects, and mastery. This model demonstrated high overall reliability, with a Cronbach’s alpha of 0.85. The scoring format uses a five-point Likert scale. In the proposed study, measurement will be conducted exclusively at the end of the intervention (Session 4) to capture the students’ overall perception of the program. Prior to analysis, items with negative wording (reverse punctuation) will be recoded so that higher scores consistently reflect a more positive experience. The statistical report will present results for both the total aggregate score and the independent mean scores for each of the six dimensions.-Player Profile: the students’ psychological and behavioral predisposition to game dynamics and narratives will be assessed using the PPDS in its validated Spanish version [21]. The PPDS is a psychometrically validated instrument composed of 21 items rated on a six-point Likert scale specifically designed to identify player profiles in the context of educational gamification based on narratives to measure the frequency of certain behaviors, where 1 means “Never” and 6 means “Always”. After a student completes the questionnaire, the system does not place them in a single category but generates five independent scores, one for each profile, showing which of the following profiles they align with the most: Tryhard (achievement- and competency-oriented); Coacher (oriented toward leadership and help); Esthetic (narrative and visual beauty-oriented); Joker (oriented to humor and surprise); or Toxic (a technical gamification term referring to players oriented toward testing system limits, seeking loopholes, or disrupting boundaries, often associated with lateral thinking rather than a negative personal judgment). The scale demonstrated high overall reliability (omega = 0.93).-Gamification Experience: Previous experience in gamification will be evaluated using the following question: Have you participated in similar activities before? The students can respond “yes” or “no”.-Sociodemographic variables: Age is understood as the time that a person has lived, counting from birth to the time of the survey, measured in whole years; gender is understood as a variable that refers to the social and cultural construction that defines the roles, behaviors, activities, and attributes that a society considers appropriate, with the answer options male, female, and non-binary; and the average grade considered to mean the average grade achieved in the first year of the nursing program to monitor the differences between the groups.-Feasibility and implementation outcomes: given the pilot nature of this trial, the following feasibility metrics will be formally tracked to inform the design of the subsequent definitive trial: recruitment rate, retention rate, technical failure rate, time-on-task compliance, and qualitative evidence of cross-contamination.

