## 4. Discussion

This protocol describes a pilot intervention designed to overcome the “one-size-fits-all” limitation in current simulation-based education. Although the literature supports the efficacy of gamification, there is a lack of reproducible methods to adapt these narratives to diverse student personalities on a large scale. The significance of this study lies in its use of Generative AI to make narrative personalization feasible and sustainable for standard nursing curricula, addressing the need for cost-effective implementation strategies. If successful, this protocol could serve as a blueprint for “Precision Education” [27] demonstrating how technology can drive the next era of personalized assessment [26]. In this model, training methodologies are tailored to the psychometric profile of the learner to maximize engagement and retention.

The necessity for such an adapted approach is underscored when comparing our proposed framework with the challenges highlighted in the recent literature. For instance, while studies [17] confirm that gamification generally enhances short-term motivation, they also warn of the ‘novelty effect’, where engagement drops if the digital environment fails to sustain a meaningful connection with the learner. Generic implementations often struggle with this, as a leaderboard that motivates a competitive student might actively demoralize a collaborative one. Furthermore, most contemporary research [20] still focuses on binary comparisons (gamification versus traditional lectures). By using generic gamification as the active control group, our protocol aims to move the conversation beyond mere technological implementation toward true precision education, isolating the specific pedagogical value of psychological profiling.

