## 5. Conclusions

This protocol presents a structured methodological framework to address the lack of personalization in simulation-based nursing education. The primary contribution of this study will be to establish the technical and pedagogical feasibility of using Generative AI to create profile-adapted clinical narratives, a process that has historically been resource-prohibitive for standard curricula.

Rather than assuming the superiority of the adapted method, this pilot study aims to provide the first empirical evidence regarding the relationship between player personality (PPDS profiles) and engagement with digital clinical cases. The data obtained will be critical to determining whether a “precision education” approach yields sufficient improvements in learning gains or satisfaction to warrant implementation in larger, randomized clinical trials.

Ultimately, the successful execution of this protocol will validate a scalable workflow for integrating psychometric profiling into the Learning Management Systems of health science faculties, potentially shifting the paradigm from “one-size-fits-all” simulations to student-centered adaptive training. By doing so, this research provides a novel and cost-effective blueprint to advance precision education in the nursing field.

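### Generative AI authoring is presented as feasible, sustainable and cost-effective, but the plan records no authoring effort, corrections or cost

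*Protocol article*

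**What the plan says.** The claims sit in three places in the protocol article.

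- **Abstract.** The background states an aim: "This study aims to validate the integration of psychometric profiling and AI as a sustainable strategy for personalized clinical training". The conclusion is a statement of fact: "The use of Generative AI makes such personalization sustainable and cost-effective for health science faculties".
- **Section 4, Discussion.** The study's significance is said to lie in "its use of Generative AI to make narrative personalization feasible and sustainable for standard nursing curricula, addressing the need for cost-effective implementation strategies".
- **Section 5, Conclusions.** The primary contribution is to "establish the technical and pedagogical feasibility of using Generative AI to create profile-adapted clinical narratives". The section closes by saying that "this research provides a novel and cost-effective blueprint to advance precision education in the nursing field".

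On how AI is used, section 2.7 says that "Generative AI is used exclusively offline during the pre-intervention design phase as a drafting tool for the narrative scripts", and that "All AI-generated texts are thoroughly reviewed, clinically curated, and validated by the PI prior to their integration into the Wix platform". Section 2.11 repeats that the PI reviews, corrects and validates all of it.

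On what is measured, section 2.8 lists the feasibility metrics as "recruitment rate, retention rate, technical failure rate, time-on-task compliance, and qualitative evidence of cross-contamination". Section 3 expects to report completion rates, time on task and bottlenecks in Wix. Section 2.10 says that the article is the full protocol and analysis plan and that there is no separate plan.

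**The concern.** The claims about sustainability and cost concern resources: how much specialist work it takes to turn AI drafts into usable clinical narratives, how often the drafts are wrong, and what the process costs. That work is finished before the first student is enrolled. The feasibility metrics begin at recruitment and follow students and the platform through the sessions, so the authoring stage falls outside them.

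If the plan is carried out exactly as written, a stated aim and the closing sentence of the Abstract will have no supporting data, whatever the learning results show. The authoring and review load, carried here by a single specialist, is also something that planners of the intended multicenter trial would need to know.

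**Working it through.** No power, alpha or sample-size figure bears on this point, and the plan gives no resource figure to reproduce. The check sets each claim against each planned source of data. The only arithmetic is a script count.

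**1. Script count.** Section 2.7 gives five narrative variations per theme in the experimental arm and a single generic narrative for each topic in the control arm. Section 2.7 also lists four thematic modules.

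- Adapted scripts: 5 × 4 = 20
- Generic scripts: 1 × 4 = 4
- Ratio: 20 / 4 = 5
- Difference: 20 − 4 = 16 more scripts to draft and check

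**2. Planned data sources against the authoring claims.**

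- Section 2.8 feasibility metrics: recruitment and retention describe participants, technical failure and time on task describe delivery, and cross-contamination describes leakage between arms. Metrics that record authoring effort, AI corrections or cost: 0 of 5.
- Section 3 reporting items (completion, time on task, Wix bottlenecks): 0 of 3.
- Other variables in section 2.8 (Learning Gain, GAMEX, PPDS profile, prior gamification experience, sociodemographics): none.
- Field diary: missing sessions and incomplete forms (section 2.9), distress, technical incidents and dissatisfaction (section 2.11), contamination (section 4.1). Authoring is not among its contents.
- Deposit of the AI prompts (section 4.2): this allows the drafting to be repeated, but gives no time, rejected drafts, corrections or cost.

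**3. Can the comparison between arms supply the answer?** Treat authoring (AI or human) and adaptation (generic or adapted) as two factors. The documents allow two readings of which scripts are AI-drafted.

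- If AI drafts the scripts of both arms, as the general wording of section 2.7 suggests, authoring is the same in both arms and the contrast is silent on it.
- If AI drafts only the experimental arm's scripts, as the Abstract suggests, authoring and adaptation change together and cannot be separated.

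On neither reading does any student receive adapted narratives written without AI. The section 1 rationale agrees: the comparator was chosen to isolate personalization.

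**4. Cost-effectiveness.** In its simplest form this is (cost in EG − cost in CG) / (Learning Gain in EG − Learning Gain in CG). The plan supplies data for the denominator. Nothing in it supplies the numerator.

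**The case against.** The strongest reply is that the formal aim and hypotheses in section 1 concern Learning Gain and satisfaction, and that cost-effectiveness is never listed as an objective. The Abstract and section 3 define feasibility as integrating AI narratives into the curriculum, and the listed metrics suit that definition. Only section 5 shifts from integrating to creating. Finishing and deploying the scripts would itself be some evidence of technical feasibility, and the prompts will be public.

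Much of this stands, and it limits the point. Several stronger readings are tempting but unsupported.

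- A reader might infer that the trial yields no feasibility data. It does yield data on delivery.
- A reader might infer that the trial undertakes to demonstrate cost-effectiveness as an endpoint. It does not. It asserts cost-effectiveness in the Abstract and in section 5.
- A reader might count the section 5 claim of a validated scalable workflow as a claim about AI authoring. That sentence concerns building psychometric profiling into learning management systems, which is a separate matter.
- A reader might turn the 16 extra scripts into extra hours. The documents give no time per script, and section 2.7 keeps the clinical content identical across versions, so reviewing five versions of one case need not cost five times as much.
- A reader might state flatly that AI authoring is the same in both arms. The Abstract and section 2.7 differ on this.

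The reply does not remove the mismatch. The Abstract names sustainability as something the study aims to validate, section 5 names AI creation of narratives as the primary contribution, and no planned measurement addresses either. A fuller analysis plan cannot be assumed, given section 2.10.

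**Conclusion.** The point holds in this limited form. Delivery feasibility is assessed. Authoring feasibility, sustainability and cost-effectiveness are claimed, but none of the five feasibility metrics, the section 3 items or the field-diary entries addresses them, and the arm contrast cannot do so on either reading of which scripts are AI-drafted.

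The known scale is 20 adapted scripts against 4 generic ones, all reviewed by one person. The count assumes one generic script per module and all five variants in each module. The workload behind it cannot be derived from the documents.

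Allocation, the primary outcome and its analysis are unaffected. What changes is what the report may conclude.

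**What to change.** Add one feasibility outcome to section 2.8, taken from a brief production log kept for each of the 20 adapted and 4 generic scripts. It should record PI time for prompting and for review, drafts rejected, clinical errors or bias problems corrected, and tool cost. State in the same place whether the generic scripts are AI-drafted, so that the Abstract and section 2.7 agree.

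Reword the Abstract, section 4 and section 5 so that sustainability and cost-effectiveness are questions the log informs rather than results already in hand.

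If the scripts were written before any log could be kept, limit the aims and conclusions to feasibility of delivery, and describe AI-authoring feasibility, sustainability and cost-effectiveness as untested assumptions. The learning-management-system claim in section 5 needs its own justification, because the log would not address it.

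The cost is a few minutes of logging per script during work already planned, some rewording, and a less favourable stated conclusion. Design, sample, randomization and the Learning Gain analysis stay as they are.

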## 1. Introduction

The use of simulation-based education to train health professionals in technical and non-technical skills has increased steadily in recent decades [1]. Within this framework, gamification has established itself as a new and rapidly growing educational methodology, especially in the academic field and in the continuous training of nurses and nursing students [2]. Gamification is widely defined as the use of game design elements in non-game contexts [3], functioning as a multidisciplinary process to improve motivation, engagement, and meaningful learning [4,5].

Gamification technologies, such as Escape Room games or immersive digital environments, involve introducing a team of players into a physical or digital space to solve puzzles in order to acquire professional skills in a complementary way to other methods [2,5]. This pedagogical approach is useful for increasing participants’ knowledge, improving their attitudes, promoting healthy behaviors, and reducing stress and anxiety [6]. In addition, it has been shown that the use of AI-driven adaptive educational games and gamified simulations promotes active learning, autonomy, and critical thinking, aligning with constructivist theories that center the learning process on the student [5,7], and can help overcome the dissonance between traditional methods and the demands of new generations of students [2]. Simulation has generally been applied successfully to improve outcomes in critical areas such as obstetric emergencies and neonatology, including reducing brachial plexus injuries and improving Apgar scores, with on-site multi-professional training demonstrating the best effect [8,9,10].

Despite the increasing adoption and demonstrated value of simulation and gamification in nursing and midwifery [11,12], there is marked heterogeneity in its implementation in different studies and programs, leading to disparities in assessment designs and tools [2,13,14]. In the context of simulation-based education, the lack of global consensus on how to assess or integrate skills is reflected in the fact that curricula are often based on the number of cases completed rather than objective outcomes [13,15]. In addition, the efficacy of educational interventions is intrinsically linked to specific characteristics such as the content, “dose”, and optimal methodology, aspects that still require identification through experimental studies [9,16]. There is a risk of the “novelty effect”, where initial motivation may decrease after the first few weeks if the challenge is not maintained or if the content is not properly adapted [17].

The lack of a personalized approach means that training often focuses on technical competence without fully integrating interpersonal skills and factors from the clinical setting, such as communication with patients and peers [15,18]. Consequently, existing programs do not always adapt optimally to individual student needs or facilitate long-term skill retention, as most studies do not perform deferred post-intervention measurements to ensure the permanence of acquired knowledge [2].

Despite the theoretical consensus on the importance of personalization, there is a notable paucity of controlled empirical studies that directly compare generic gamification and adapted gamification, with more studies [19,20] investigating gamification versus non-gamification. Personality traits fundamentally shape student engagement, intrinsic motivation, and responsiveness to gamified interventions, as different player typologies react differently to specific game mechanics. To address the need for personalization and homogenization in gamification-based training, this study proposes the implementation of an adaptive model integrated with standardized assessment tools. Specifically, the Player Personality and Dynamics Scale (PPDS), validated in Spanish, will be used to identify player profiles in educational gamification contexts with narrative elements [21]. While various classifications of player profiles exist in the literature, the PPDS was specifically selected for this protocol because it is already adapted and psychometrically validated in Spanish. Applying non-adapted frameworks to our specific student cohort could introduce linguistic and cultural biases, making the PPDS the most methodologically rigorous choice available to ensure measurement accuracy in this context.

These adaptive models are crucial because evidence suggests that the most effective interventions are those that include multiple components and can tailor the narrative to individual needs [22,23]. In healthcare education, the incorporation of advanced high-fidelity simulators with structured feedback mechanisms and continuous assessment is vital to refining technique and fostering clinical decision-making skills [24]. Recent innovations include using artificial intelligence for adaptive responses in simulation environments, indicating a trend towards personalized and sustainable competency-based training strategies [25]. This paradigm shift aligns directly with the emerging concept of ‘Precision Medical Education’, which emphasizes the use of technology and continuous data streams to tailor educational trajectories to the specific needs of each learner [26,27]. Employing an approach that combines individualized measurement, through the PPDS [21], with adaptability enables the design of personalized gamified experiences that improve learning and interaction in the classroom, optimizing professionals’ ability to acquire the necessary competencies [14] and improve their quality of care in clinical practice.

Current research has reached a saturation point regarding the general efficacy of gamification versus traditional methods, yet a critical gap remains in understanding how to optimize these interventions for diverse types of learners. Generic gamification carries inherent risks: if the game mechanics do not align with the student’s intrinsic motivation, it can lead to frustration, cognitive overload, or disengagement, potentially mitigating the educational benefits.

This study is necessary and timely because the recent maturation of Generative Artificial Intelligence (AI) finally enables scalable and sustainable personalization of clinical narratives—a feat previously considered too resource-intensive for standard curricula. The novel and testable contribution of this protocol is the shift from a binary comparison (game vs. no game) to a nuanced analysis of mechanics–profile fit. Therefore, generic gamification was chosen as the active comparator to isolate and quantify the specific added value of the ‘personalization’ variable.

Consequently, the aim of this study is to evaluate the effectiveness of a profile-adapted gamified intervention compared to a generic gamified intervention in improving the academic performance of nursing students regarding obstetric competencies upon completion of the four-week program. Based on this aim, the following hypotheses are proposed:-Primary hypothesis—the Experimental Group (EG), with exposure to the profile-adapted narrative, will demonstrate a significantly higher global Learning Gain (LG) compared to the Control Group (CG) receiving generic gamification.-Secondary hypothesis—there is a positive correlation between the level of student satisfaction and academic performance (LG) regardless of the group.

